#### Ethical consideration and consent/assent process

Prior to administering the survey, respondents will be asked for their consent, using standard format forms. Surveys will be administered in a private room/safe space in the participant’s residence/community and will last approximately 45–60 mins (based on our pre-testing experience). To protect participant privacy and ensure confidentiality, all Personally Identifiable Data (PID) will be appropriately stored and secured in accordance with the data security measures. All survey forms will only contain a unique ID code generated for the study.

Due to the sensitive nature of questions being asked, participants may feel personal discomfort, fatigue, or embarrassment during survey administration. Participants will be reminded that their participation is completely voluntary. They do not have to answer any question that they do not feel comfortable answering, and they can decide to end their participation in the study at any time. We do not anticipate respondents to be subjected to more than a minimal risk of discomfort from participating in this study. Additionally, our secure storage, encryption, and coding of all data, particularly PID, serves to minimize any risk of breaching confidentiality and compliance with local data privacy law.

Study participants will be able to access the game for free directly from their own Google Play Store account. Once downloaded the GNG game has clear terms of service that need to be accepted by the player, including preconditions for downloading the game if the person is under the age of 15. Participants who do not own their phones or share their phones with family members, may run the risk of backlash from male members/parents who may have reservations about access to SRH information among adolescent girls. In this regard, we will recruit credible community members and peers who are tasked to brief parents about the goal and objectives of the game, and the content will be aligned with the curriculum outlined in the government program for adolescents.

#### Confidentiality

All steps to ensure that participants’ information will be kept confidential by trained study staff to ensure that collected information will be secured and will not be shared with others. In the event that we find out through the study that participants are at risk of harm or there is a risk of harm to others, we will need to break confidentiality in order to provide an active referral for services, and/or report this risk to the relevant authorities (Indian Sigma Institutional Review Board (IRB) and the international Population Council IRB). We will ensure that participants understand that they can refuse to answer any question or stop participating in the study at any time.

#### Data security

To effectively monitor participants over the study period, identifiable data on participants’ demographic backgrounds, and personal contact information (household addresses, phone numbers, and e-mails) will be collected as part of the in-person survey. The data collected from in-person surveys will be administered in an electronic Computer Assisted in-Person Interview (CAPI) format, using the CSPro survey management system utilized by the U.S. Census Bureau [17]. Electronic survey data will be collected by interviewers on Android-based tablets, and data will be securely transferred from the Android tablets onto an Amazon Web Services (AWS) supported, secure, cloud server at the end of each working day. All Android tablets will be used for data collection only, and tablets’ settings will be adjusted so that field staff is blocked from accessing applications that are not applicable for data collection (e.g., internet browsing, social media, email). The AWS cloud server will be HIPAA-compliant and will meet all the necessary security requirements for storing Level 4 identifiable data. Once the data has been securely transferred to the cloud server, the survey record on the Android tablet will be immediately erased.

#### Informed consent process

Participants who are under the age of 18 are minors who cannot voluntarily provide consent for themselves, and therefore, will require parental consent with participant assent to participate in the study. All consent and assent processes with parents and adolescents will be administered in person, following household listing and recruitment of eligible households. Some members of this population may be subject to the influence of others, particularly parents and other elder members of the household, due to power relationships internal to the household and/or the community.

### Follow-up survey

Following the ten-week intervention period/encouragement, participants will be assessed through the administration of the follow-up survey. All procedures related to informed consent, confidentially, data privacy, and risk mitigation will be followed, as will been done in the baseline. Resurveying participants in this manner will enable us to create a panel of individual girls, in which each girl is observed over two time points. In the endline survey, we will collect data using the same survey tool, with an additional section on gameplay and game-related elements, including brand recall of in-game links to products and services.

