**Methods:**

A two-arm RCT will be conducted in three cities in India: Patna, Jaipur, and Delhi-NCR. The first arm is the treatment (encouragement) arm (n = 975) where the participants will be encouraged to download and play the game, and the second arm (n = 975) where the participants will not receive any nudges/encouragement to play the game. They may or may not have access to the game. After the baseline recruitment, participants will be randomly assigned to these two arms across the three locations. Participants of the treatment/encouragement arm will receive continuous support as part of the encouragement design to adopt, install the game from the Google Play Store at no cost, and play all levels on their Android devices. The encouragement activity will continue for ten weeks, during which participants will receive creative messages via weekly phone calls and WhatsApp messages. We will conduct the follow-up survey with all the participants (n = 1950) from the baseline survey after ten weeks of exposure. We will conduct 60 in-depth qualitative interviews (20 at each location) with a sub-sample of the participants from the encouragement arm to augment the quantitative surveys.

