## Baseline and follow-up survey tools

### Quantitative survey

After completing the household listing exercise, the eligible participants will be identified and listed with the help of a screening tool. The final list of respondents will be prepared after de-identifying the individual participants into unique identification respondent IDs. For the main phase RCT study, we will recruit adolescent girls based on the previously mentioned inclusion criteria. The final list will be considered the sampling frame for the recruitment of baseline data collection. Once the sampling frame is developed, the eligible adolescent girls will be approached for data collection of in-person surveys.

The survey tool was prepared and tested in the pretesting of the method. There are eight sections in the baseline questionnaire and nine for the endline. (See Table 3).

**Table 3 Tab3:** Sections in the survey tool

Section	Theme	Description
I A	Household Characteristics	Details of household features, including understanding socio economic level of the household related to household goods/financial condition
I B	Individual Characteristics	Background information on age, siblings, parents, education, livelihood, friends, and career aspirations
II	Media and Technology	Phone and media consumption patterns
III	Health Services Utilization	Availability, accessibility, and preferences for healthcare services
IV	Menstrual Health and Fertility Awareness	SRH information/services received, perception, and attitude towards MHM
V	Empowerment and Aspirations	Understanding of personal aspirations, knowledge/attitudes about career aspirations, preparation for job/career, and financial independence
VI	Negotiation and Consent	Knowledge of attitudes and perceptions towards personal agency, consent in relationships, the legal age of marriage, and consent for sex
VII	Male and Female Relationships	Age-appropriate questions on types of relationships (platonic/physical), attitudes towards dating, perception of acceptable activities in a relationship
VIII	Contraception	Knowledge of methods of contraception, accessibility, and utilization
IX Only for endline survey	Knowledge, Attitude, and Practices: Go Nisha Go	Knowledge of GNG game, levels played, links accessed, product and brand recall, gameplay, and intention for behaviour change and measurement of confidence for negotiation with partner/parents

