#### Data safety, monitoring, and protection for human subjects

We will develop our study protocol in accordance with the guidelines provided by the institutional review boards. We will strictly follow the ethical consideration to maintain encouragement of the study participants in the treatment arm. Regarding the data safety and monitoring of the study participants, we will focus on three major aspects: (a) assurance of no harm reaches the study participants to take part in the study, (b) assurance of data security—no PID is collected and shared to maintain the privacy of study participants (c) assurance to minimize risk for the commencement of adverse events. The study participants will be provided with the state’s helpline numbers and the community level organizations will be involved to safeguard participants.

Should there be an occurrence of any adverse events, the principal investigators of India will be informed within 72 h. The field investigators will be trained in handling situations at the community level, where maintenance of confidentiality and privacy is imperative to the study. The study team will continuously work on reducing risk and harm if caused during the study period. The principal investigator and senior researcher will diligently monitor and provide guidance to the field teams. As mentioned earlier, data collected will have no personal identifiers in the data. The data will be uploaded in AWS secure cloud server on a real time basis. All study computers used for descriptive analysis of the de-identified data will be password protected, and only study staff who are cleared to view the data will have the password. All study data and linking keys will be password protected at all times. All electronic files will be backed up nightly to minimise the likelihood of lost files or data. All electronic data, both on the AWS secure cloud server and on any study computers, will be encrypted and password protected. Identifiable hard-copy data, including signed consent forms, will be collected and stored in a locked cabinet in access-limited rooms at the office. The information key will only be accessible to the research team.

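### Family backlash is named as a risk of game access, but as described no survey section or outcome measures it, and reported harms could not be reliably compared between arms

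*Protocol article*

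**What the plan says.** All references are to the protocol article.

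- **Named risk.** Under Ethical consideration and consent/assent process, girls who share or do not own a phone "may run the risk of backlash from male members/parents who may have reservations about access to SRH information among adolescent girls". The Recruitment section admits girls with a shared device, so this group is enrolled by design.
- **Endline tool.** Under Follow-up survey: "we will collect data using the same survey tool, with an additional section on gameplay and game-related elements". The Quantitative survey section agrees: "There are eight sections in the baseline questionnaire and nine for the endline". The description of the added Section IX in Table 3 begins "Knowledge of GNG game, levels played, links accessed, product and brand recall, gameplay, and intention for behaviour change" and ends with confidence in negotiating with a partner or parents. No Table 3 description mentions backlash, phone restriction or adverse events, and Table 4 lists no harm outcome.
- **Adverse events.** Under Data safety, monitoring, and protection for human subjects: "Should there be an occurrence of any adverse events, the principal investigators of India will be informed within 72 h". The Confidentiality section provides for referral or reporting if the study finds that someone is at risk of harm. No scheduled enquiry is described.
- **Contact between surveys.** In the encouraged arm, over ten weeks, "participants will receive creative messages via weekly phone calls and WhatsApp messages". In the other arm "the participants will not receive any nudges/encouragement to play the game". Both arms have in-person surveys at baseline and after ten weeks.
- **Interviews.** The 60 in-depth interviews come from the encouraged arm only (Sample size). Their listed aims (Qualitative in-depth interviews) do not include backlash.

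**The concern.** The harm that the protocol itself ties to access to the game is one it does not describe measuring. What remains is passive reporting. A passive route serves the individual girl, but it gives a fair comparison between arms only if girls in both arms have a similar chance to be heard. Here one arm has about ten scheduled weekly calls and the other has none described between surveys. Calls to a shared phone may also be a poor place to disclose conflict at home, so under-reporting is possible in the encouraged arm too. The direction of the net error is not known.

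The study is meant to support scale-up of a game delivered straight to girls, many of them possibly on family phones. Few or no adverse events would say little about backlash, and an excess in the encouraged arm could not be separated from more frequent contact. The efficacy comparison is not affected.

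**Working it through.** **1. Figures in the document.** 3 × 325 = 975 per arm, and 3 × 650 = 2 × 975 = 1,950, as stated. No harm rate, disclosure rate or dropout rate is given. Every rate below is an assumption for illustration.

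**2. Passages side by side.** The risk is stated, the endline content is fixed as the baseline tool plus a gameplay section, the Table 3 and Table 4 descriptions do not cover the risk, the adverse-event route waits for an occurrence, and interim contact is scheduled in one arm. Together these give no harm measure collected in the same way in both arms.

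**3. Unequal detection with equal true risk.** Expected reports = 975 × true risk × share detected.

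- 5% true risk, 80% v 20% detected: 975 × 0.05 = 48.75; × 0.8 = 39; × 0.2 = 9.75. Apparent ratio 4.0.
- 5%, 80% v 40%: 39 v 19.5. Ratio 2.0.
- 2%, 80% v 20%: 15.6 v 3.9. Ratio 4.0.

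Chance that a two-sided 5% test would call such a difference significant, with n = 975 per arm: Φ[(d − 1.96·se₀)/se₁], where se₀ uses the pooled proportion and se₁ the separate ones. For the first case the reported proportions are 0.04 and 0.01:

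- d = 0.03
- se₀ = √(0.025 × 0.975 × 2/975) = 0.00707
- se₁ = √[(0.04 × 0.96 + 0.01 × 0.99)/975] = 0.00704
- (0.03 − 0.01386)/0.00704 = 2.29, so Φ = 0.99

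The second and third cases give 0.74 and 0.76.

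**4. Passive against direct enquiry (Fisher exact test, 975 per arm).**

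| Assumed true risk | Assumed reporting | Expected reports | p |
|---|---|---|---|
| 3% v 3% | volunteered by 60% v 10% | 18 v 3 | 0.0014 |
| 6% v 3% | volunteered by 10% in both arms | 6 v 3 | 0.51 |
| 6% v 3% | asked directly, 80% disclose | 47 v 23 | 0.0048 |

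The first row is a false signal. The second misses a true doubling through low reporting alone, without unequal contact. The third recovers it.

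**5. What equal enquiry at endline could show.** Same formula, with the rates read as the proportions reported. For 2% v 4%: d = 0.02, se₀ = √(0.03 × 0.97 × 2/975) = 0.00773, se₁ = 0.00771, and (0.02 − 0.01514)/0.00771 = 0.63, so power is 74%.

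| Reported proportions | 975 per arm | 780 per arm (assumed 20% loss) |
|---|---|---|
| 1% v 2% | 44% | 37% |
| 2% v 4% | 74% | 64% |
| 5% v 10% | 99% | 96% |
| 10% v 15% | 92% | 85% |

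Equal enquiry would thus be informative for moderate rates and weak for rare events.

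**The case against.** The strongest objection is that this is a condensed article. Table 3 gives one line per section, not items. The encouragement schedule (Table 1) was not readable and the call scripts are not reproduced. A backlash question may exist in the questionnaire or the scripts. This stands, and it limits the point to what is described.

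The safeguards also deserve credit. Community members and peers brief parents, which answers the backlash risk directly. Helplines go to study participants without restriction by arm, field staff are trained, and harm found in either arm is referred or reported. These protect individuals but do not produce a comparison between arms.

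Four stronger readings may tempt a reader, and the documents do not support them:

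- *The trial cannot tell whether encouragement harms girls.* Without the item-level questionnaire this goes too far.
- *The trial leaves a second named harm of the game, distress, unmeasured.* The text says "participants may feel personal discomfort, fatigue, or embarrassment during survey administration". That is a burden of the survey, shared by both arms, and does not bear on encouragement.
- *Controls have no staff contact.* They have two in-person surveys in a private or safe space. What is not described is contact between them.
- *The trial will report a false harm signal.* That would need a between-arm test of adverse events, and none is planned in the text. The figures above show only why such a comparison would be unsafe.

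Finally, the endline is not free of bias. Researchers are not blinded, the Data analysis plan expects some missing follow-up, and girls facing backlash may be among those lost. This stands as a limit on the remedy.

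**Conclusion.** The point holds as a cheap improvement, not as an error that undermines the trial. As described, a risk that the protocol attributes to game access is in no survey section or outcome, adverse events are captured only reactively, and scheduled interim contact exists in one arm only. Reported harms could therefore not be reliably compared between arms. This rests on section-level descriptions; an item not listed in the article would weaken or remove it.

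The size is unknown. Under the assumed detection shares for the 2% and 5% risks in step 3, unequal contact alone gives apparent ratios of 2 to 4 with no true difference. These are illustrations, not estimates.

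**What to change.** Add to the endline interview, outside Section IX and worded identically in both arms, a few questions about the period since the baseline survey. Suitable topics are family conflict over phone use or health information, the phone being taken away or restricted, and movement or schooling being restricted. Handle positive answers through the existing route in the Confidentiality section.

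Report these items by randomised arm as the harms comparison, and state unblinded interviewers and loss to follow-up as limits. List events volunteered on encouragement calls separately, without comparing arms. If the questionnaire already holds such items, say so in the outcome list and apply the same reporting rule.

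The cost is a slightly longer interview (now about 45–60 minutes), a change to the electronic form, notice to both ethics boards after the partners agree (Ethics approval), and some additional referrals. No extra visits are needed, because both arms already have an in-person endline interview.

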#### Qualitative in-depth interviews

After the follow-up survey, we will administer in-depth interviews (IDI) with a sample of 60 adolescent girls from the three study sites (20 girls per site). The purpose of the qualitative interviews is to complement the quantitative data analysis, to improve our understanding of adolescents’ experiences with the GNG game, such as: (1) Gain better understanding of the SRH environment for adolescents, including established gender norms, expectations around relationships and intimacy between adolescent girls and boys, and attitudes towards sex, marriage, girl’s health—including MHM, fertility awareness, contraception, and pregnancy; (2) Assess the level of access and availability of menstrual and contraceptive knowledge, information, products, and services through the DTC approach; and (3) Evaluate the agency and level of confidence for intended behaviours related to improved SRH outcomes, such as decision making and consent, and negotiation for delaying early marriage and pregnancy.

As with the quantitative surveys, we will explain the purpose of the interviews to participants of the qualitative survey, taking consent/assent before starting the interview. Girls will be selected for the personal IDIs in accordance with the inclusion and exclusion criteria. Interviews and debriefing activities will be administered in private rooms, or outdoor areas where privacy can be assured, and will last approximately one hour per participant. Interviews will be conducted in Hindi. Some interview questions will be open-ended, although most of the interview will follow the interview guide, which will help to ensure that key questions will be asked, and key domains will be addressed.

The in-depth interviews will be conducted by trained qualitative female research investigators between the ages of 21 to 30 years. All interviews with the participants will be digitally taped by the interviewers using audio recorders. If the participants refuse this process, we will administer the note-keeping process during the interview. After completion of the interviews, the investigator will save the audio recording in the protected computer system﻿, CAPI, assigned by the study team. The interview notes will be translated into Hindi and into English, then labelled and stored in the same interview folders on the computer. After completion of each interview, the audio recordings will be translated from Hindi to English, transcribed, and labelled. In case of non-availability of the audio recording, the interviewer will make a copy of notes from the interview, label, and save it in txt. format on the computer. All PID will be removed from interview forms and a unique ID number will be assigned. Coded forms will be kept separate from the code list to maintain confidentiality.

All linking files will be stored separately in a locked cabinet at the Data Collection site. Audio recordings of the interviews and related data will also be stored separately from the transcripts of the interviews. Both recordings and transcripts will be stored in a locked facility. All study members will be trained in maintaining participant confidentiality.

#### Outcomes measures

The baseline and follow-up survey tools are created with the previously tested tools from standard studies such as the UDAYA study (Understanding the lives of adolescents and young adults) [3], National Family Health Survey (NFHS) [18], Comprehensive National Nutrition Survey (CNNS) [19], Living Standards Measurement Study [20], and other national surveys in India [21]. The primary outcome of the evaluation is to measure improvement in the existing knowledge of MHM, contraception, and increased in agency for adolescent girls making informed decisions and choices in their lives (See Table 4). Several other secondary outcomes measuring intended behaviour change and agency with respect to improvement in decision making, choice of career, negotiation in relationships, and assertion of self-identity will also be evaluated.

**Table 4 Tab4:** List of selected outcome indicators for the study

Outcome indicators	Contents of measurement
Menstrual health management	Percentage of girls who have: - Received any information about MHM - Awareness about sanitary napkins - Awareness about different menstrual hygiene products - Obtained menstrual products alone - Practiced tracking their menstruation with comprehensive understanding of fertility awareness - Experienced trouble in obtaining menstrual hygiene products - Bought menstrual hygiene products online
Contraception	Percentage of girls who have: - Awareness about modern contraceptive methods - Comprehensive knowledge about Oral contraception pills - Comprehensive knowledge about Emergency contraception pills - Comprehensive knowledge about condoms - Comprehensive knowledge about IUD - Comprehensive knowledge about injectables - Practiced refusing sex due to non-availability of contraception - Awareness about condom’s use for prevention of pregnancy and/or infections
Agency (decision making, negotiation, and consent)	Percentage of girls who/ have: - Gone to college on their own/alone, - Believe that “girls should make decisions for themselves”, - Believe that “girls can wear what they want”, - Believe that “girls should manage their own money”, - Believe that “girls should be financially independent”, - Believe that girls can talk to their parents when they were asked to marry a person whom they do not want to marry, - Feel confident to say no to a sexual act, - Feel confident to use condoms when her boyfriend is not willing to, - Think their boyfriend should always take consent for sex and refuse sex due to non-availability of contraception

